### Questionnaire data

#### Sampling

Participants will be approached through the data trustee of the evaluation team, who is the only one with access to the physicians’ practice and patients’ contact addresses for the surveys. With their enrolment into the MamBo-care model, each participating physician, practice staff and patient receive a written letter of consent to participate in the first and second surveys. Addresses of physicians who are members of the physicians’ network but do not participate in MamBo will be provided by the CM to the trustee. The written declaration of consent and the questionnaire will be sent out in parallel. In order to guarantee high quality, standards for the questionnaire development [14–16] methods of pretesting [17] and the Dillman’s Total Design Method for achieving a possibly high response rate [18] were used.

Since the given consent of the physicians’ survey in the first study year was approx. 50% and is a lot lower in the practice staff survey, a response from approx. 20 and 40 participants are expected for t0. The first questionnaire of all participating physicians and their practice staff started in the first half of 2018. The non-participating physicians survey was conducted in summer 2019 (*n* ~ 60).

The t0 questionnaire of patients shows a very high consent rate and a response rate of approx. 80%. With the high response rate and incentives provided, low panel attrition is expected (approx. 20%). As an incentive, a postage stamp is enclosed with the t1 questionnaire. The survey of patients also started in the first half of 2018. The last enrolment for the t0 questionnaire will be in April 2020 (n ~ 1900), accordingly approx. 1500 patients will be surveyed at both, t0 and t1.

#### Data collection and analysis

To determine the perceived benefits of the care model the physician survey includes expectations of the care model (t0) or rather the fulfilment of expectations (t1). Besides that, practice characteristics (e.g. number of MFAs, joint practice/single practice) and process data (e.g. workload, information procurement) are collected. In the survey of non-participating physicians, reasons for non-participation are collected additionally. By distinguishing between participating and non-participating physicians, but also between “early adopters” and “late adopters”, it can be determined whether and if so which characteristics are significantly different between these groups. With the second survey, a pre-post comparison is possible to examine which factors have changed as a result of participation.

With the first patient survey (t0), sociodemographic characteristics, health-related characteristics (e.g. state of health, mobility, well-being), general characteristics (e.g. social support, coping, living environment), satisfaction with previous care, reasons for participating in MamBo and expectations are recorded. Translated and validated standard scales used in the physicians and patients surveys are listed in Table 2.

**Table 2 Tab2:** Standardized scales used in the postal surveys

Scale	Outcome

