**Discussion:**

A new form of coordinated care has been introduced to improve intersectoral care of multimorbid patients and reduce the workload on physicians. The effects of the MamBo care model are being investigated for patients, physicians and the cost units. The results will form the basis for the decision whether the care model should be transferred to standard care and what needs to be taken into account for implementation.

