## Methods/design

### Setting

The new care model MamBo is introduced in a physician’s network in the region of Leverkusen, a small metropolis in North Rhine-Westphalia (Germany). The implementation takes place in established general practitioners or specialist practices. Only physicians who are part of the physicians’ network can participate in MamBo. Currently, it is estimated that approx. 40 physicians and approx. 160 practice staff will participate in the care model. Inturn, approx. 2615 multimorbid patients with at least three chronic diseases and insured with PronovaBKK will be recruited by the participating physicians for the MamBo program. Patients in oncological or palliative treatment are excluded. The initial period of the MamBo-project was set for 3 years (07.2017–06.2020). After applying for an extension of 9 months, due to delays at the start of the study and initial recruitment difficulties, the study now ends on 31 March 2021.

The presented study is a multiperspective evaluation study including a qualitative and a quantitative evaluation design. Qualitative data for process evaluation and quantitative data for outcome evaluation are collected simultaneously. Different domains of the quantitative and qualitative evaluation design are listed in Table 1.

**Table 1 Tab1:** Different domains of the multiperspective evaluation study

Evaluation type	Data source		time of data collection
Process evaluation	focus groups	participating physicians	annual, during the intervention phase
		monitoring and coordination assistants	
	semi- structured interviews	demand management	
		care management	
		management consultancy	once after the implementation
Outcome evaluation	primary data	questionnaire of participating physicians (n ~ 40)	two time-points during the intervention phase
		questionnaire of participating practice staff (n ~ 160)	
		questionnaire of participating patients (t0: n ~ 2460; t0 & t1: n ~ 1500)	
		questionnaire of non-participating physicians within the physician’s network (n ~ 60)	one time-point during the intervention phase
	secondary data	statutory health insurance claim data (group 1: n ~ 1.975; group 2: n ~ 2524)	during and at the end of the intervention phase
		RGL- process data	

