### Quantitative evaluation

#### Quantitative evaluation design

In order to measure effectiveness and treatment effects, postal survey data of all physicians, practice staff as well as patients enrolled in MamBo, will be conducted as a longitudinal study with two time-points. The first questionnaire (t0) is surveyed immediately after the enrolment into the project. The second questionnaire (t1) was originally surveyed 1 year later. As we had difficulties in reaching the required number of patients, the funder proposed to change the intervention period from 1 year to 6 months in the course of the extension application. Due to the fact that the majority of the MoniKa intervention takes place within the first 6 months after enrolment in MamBo and that the MamBo structure is more established in 2020 than in previous years, the evaluation team assumes that a comparison of the groups is still possible and agreed to shorten the period of patient examination. Patients enrolled after November 2019 will, therefore, receive the t1 after 6 months.

Depending on the doctors’ assessment of the patients’ health condition and needs as well as the patients’ wishes, the included patients receive either a MoniKa-home visit, a short MoniKa-call or no MoniKa contact at all. The latter do not receive an additional new form of care and will be considered as the non-treatment group. However, it is expected that they profit indirectly from the MamBo structures on the organisational level. Thus, the patients’ survey can be defined as a cohort study with follow-up and a non-randomized treatment. Non-participating physicians will also be surveyed cross-sectional.

To evaluate the cost-efficiency and effectiveness of the care model secondary claim data will be used. For this, a quasi-experimental cohort study will be conducted. Multimorbid patients (control group) will be compared with multimorbid MamBo-patients (intervention group).

In addition, documentations of the physician network with records of the process-data of the CM provides information about the implementation process.

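### The participating physicians' before-after change is attributed to participation, but non-participating physicians are surveyed only once, so no background trend can be separated from MamBo

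*Protocol article*

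**What the plan says.** The Abstract (Discussion) gives reducing physicians' workload as one of two purposes of the care model and adds: "The effects of the MamBo care model are being investigated for patients, physicians and the cost units". Quantitative evaluation design introduces the surveys of physicians, practice staff and patients as the means of measuring effectiveness and treatment effects.

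Table 1 (Setting) lists about 40 participating physicians and about 160 practice staff, surveyed at "two time-points during the intervention phase". About 60 non-participating physicians of the same network are surveyed at "one time-point during the intervention phase". Quantitative evaluation design confirms this: "Non-participating physicians will also be surveyed cross-sectional". Under Questionnaire data, Sampling, that single survey is dated to summer 2019, whereas the participants' first questionnaire began in the first half of 2018. The same section reports consent of about 50% among physicians and much less among staff, so that "a response from approx. 20 and 40 participants are expected for t0" (physicians and staff respectively).

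Under Questionnaire data, Data collection and analysis, the contrasts between participants and non-participants and between early and late adopters serve to find which characteristics differ. The repeat survey of participants then gets a causal reading: "With the second survey, a pre-post comparison is possible to examine which factors have changed as a result of participation".

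**The concern.** A change measured only in those who joined is the sum of any effect of joining and everything else that moved over the interval, such as general workload trends or changes in the practice. To separate the two, the change must also be known in physicians who did not join, and the plan collects no such change. It would nevertheless report the whole movement as what participation brought about.

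The article says that the results will inform a political decision on transfer to general care, and relief of physicians is one of the model's selling points. An uncontrolled change labelled as an effect could be carried into that decision. Conversely, with about 20 respondents, the absence of a visible change would say little.

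**Working it through.** **1. Is there a controlled change for physicians or staff anywhere?**

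| Planned element | Whom it concerns | Controlled change for physicians or staff? |
|---|---|---|
| Participant survey, t0 and t1 | Participating physicians and staff | No, one group only |
| Non-participant survey | About 60 network physicians, once, summer 2019 | No, one measurement gives no change |
| Early versus late adopters | Both groups participate | No, used to compare characteristics |
| Difference-in-differences with inverse-probability weights | Patients, by MoniKa contact | No |
| Propensity-score twins in claims data | Patients | No |

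The Discussion section names selection bias, the willingness of interviewed physicians and the 6- versus 12-month interval among patients as limitations. It does not name the missing concurrent change.

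**2. Size of the bias.** Let the true effect be E and the background drift D. The mean pre-post change in participants estimates E + D. With E = 0 it estimates D, whatever the sample size.

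**3. How often would drift alone look like an effect?** The article gives no test, significance level, SD or power for the physician survey, so there is no figure of its own to reproduce beyond the respondents: 40 × 50% = 20, as stated.

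Assumptions: paired t-test, two-sided 5%, E = 0, equal SD at t0 and t1, drift in SDs of the score, t0-t1 correlation r from 0.4 to 0.8. Then

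- SD of change = √(2(1 − r)): 1.095, 0.894 and 0.632 for r = 0.4, 0.6 and 0.8.
- Noncentrality = (D / SD of change) × √n. For D = 0.3, r = 0.6, n = 20: 0.3 / 0.894 = 0.335, and 0.335 × 4.472 = 1.50.
- The probability of significance comes from the noncentral t distribution with n − 1 degrees of freedom.

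| n = 20, no MamBo effect | r = 0.4 | r = 0.6 | r = 0.8 |
|---|---|---|---|
| Drift 0.1 SD | 7% | 8% | 10% |
| Drift 0.3 SD | 21% | 30% | 52% |
| Drift 0.5 SD | 49% | 66% | 92% |
| Change detectable with 80% power | 0.72 SD | 0.59 SD | 0.42 SD |

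The last row is 0.660 × SD of change. If 16 of the 20 return t1 (applying to physicians the 20% attrition that the article expects for patients), the detectable change at r = 0.6 is 0.67 SD. For 40 staff, a 0.3 SD drift at r = 0.6 is significant in 54% of studies.

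**4. What would a repeat survey of non-participants add?** If both groups drifted equally, the difference in changes would have mean zero and a simulated rejection rate of about 5%, as it should. The cost is precision. At r = 0.6 the detectable difference with 80% power is 0.74 SD for 20 versus 30 physicians (0.825 × 0.894) and 0.66 SD for 20 versus 60 (0.732 × 0.894), against 0.59 SD for the uncontrolled change.

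**The case against.** The strongest reply is that this is one phrase about a secondary survey. The primary survey outcomes are patient-reported, and the only sample-size calculation belongs to the claims data. The physician survey is introduced as a way to learn about perceived benefits through expectations at t0 and their fulfilment at t1. The fulfilment items ask about MamBo itself, so drift matters much less there. Focus groups, interviews and network process data also bear on physicians' experience. All of this stands, and it limits the point to repeated measures such as workload, burden and perceived safety. None of these sources supplies a controlled change in those measures.

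A second reply is that the percentages rest on a decision rule the article does not state. That also stands: for the physician pre-post comparison no paired t-test or 5% rule is given, and nothing in the article shows that a drift of 0.3 or 0.5 SD is likely. The percentages are illustrations. The one-to-one bias in the estimate needs none of these assumptions.

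Three stronger readings are tempting but not supported:

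- A reader might infer that regression to the mean is at work. Physicians join as members of the network, and nothing says they were selected for high workload or burden.
- A reader might infer that the pre-post comparison is the only evidence on physicians. It is the only quantitative analysis of change, not the only source.
- A reader might infer that surveying the non-participants again would repair the design. It would not fully: their first measurement dates from summer 2019, while participants' t0 began in the first half of 2018.

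**Conclusion.** The causal wording goes beyond what the design can support. In repeated physician measures, the planned comparison credits any background trend to MamBo in full. The sentence on participation is in the physician paragraph, but the staff survey has the same two-time-point design and no non-participating staff are surveyed, so staff changes could not carry an effect claim either.

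This conclusion rests on the article's own text: the attribution, the single non-participant survey, and the restriction of the controlled analyses to patients. An unseen analysis plan could refine the model but could not create a second measurement in non-participants that the article says is not taken. How often drift would be declared significant is assumption-dependent: with 20 physicians, about 7% to 10% for a 0.1 SD drift and 21% to 52% for 0.3 SD.

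The correction is worth making because the claim concerns a stated aim of the model and may feed a decision on standard care. It does not touch the primary patient outcomes or the claims analysis.

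**What to change.** 1. In the physician paragraph of Questionnaire data, Data collection and analysis, replace the clause that attributes the change to participation by wording such as: change since joining.
2. Report physician and staff changes descriptively with 95% confidence intervals. Do not present them as effects of MamBo on physicians, and bring the Abstract's statement on effects for physicians into line.
3. Add to the limitations in the Discussion section that no concurrent change was measured in non-participating physicians or staff.

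This needs no new data. The price is a less favourable claim.

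A second mailing to the approximately 60 non-participating physicians is optional only. About 12 months after summer 2019 would fall before the study ends on 31 March 2021. It would measure 2019-2020 and not the interval of physicians who enrolled in 2018. It has lower power (about 0.66 to 0.74 SD detectable at r = 0.6, if 60 or 30 give both measurements), and may need new consent and linkage to the 2019 responses. The groups would remain self-selected, and staff would still have no comparator. If it is done, these limits should be stated with the result.

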**Physicians survey**	
HSOPS_M Hospital Survey on Patient Safety Culture for Hospital Management - overall perceptions of safety) [19]	patient safety
Dispositional Resistance to Change Scale - routine seeking [20]	openness to innovations
The workload in Nursing scale captures - psychophysical overload [21]	psychophysical burden of workload
**Patients survey**	
WHO 5-items Well-being Scale [22]	wellbeing
PACIC - Patient Assessment of Chronic Illness Care shortened form [23]	patients’ perceptions of the quality of care they have received for their chronic conditions
EFK-HPC Questionnaire on Disease Processing - Acting, problem-oriented Coping [24]	current coping efforts
Patient questionnaire of cologne (subscale) [25]	burden of disease
HL-COM -Health Literacy sensitive Communication [26]	health literacy sensitive communication
Medication Adherence Rating Scale (MARS) [27]	drug compliance
BS6 - Brief Social Support Scale (BS6) [28]	social support
PHQ-2-Patient Health Questionnaire 2 [29]	depression
EORTC-QLQ-C30 (subscales) [30]	quality of life regarding physical function and global health

In the second survey (t1) only the time-variant measures remain. In addition, questions regarding life events and the MamBo-intervention are added. Primary outcomes are patients’ perceptions of the quality of care, social support, drug compliance and wellbeing. The analysis of the survey at t0 examines whether and in which characteristics participating patients differ from each other at their point of enrolment. With the second survey, a pre-post comparison within one group and a pre-post comparison between the treatment groups and the non-treatment group will be possible.

For data preparation, Tele-form® software has been used. The quantitative data will be analysed using regression-based methods. Structural Equation Modeling (SEM) is used to study intermediate social factors. Difference-In-Differences (DiD) estimation are used to inspect the effect of the MoniKa intervention on e.g. patient satisfaction. Confounder adjustment will be achieved by using inverse-probability weights (IPW), to adjust for the probability of being visited by a MoniKa (treatment group). Various covariates will be specified as confounders like patients’ morbidity characteristics (patients’ mobility, age and years of being chronically ill). In addition, the patients’ trust in the physicians will also be accounted for. To assess comparability, a subgroup analysis will be performed between patients who completed the t1 questionnaire after 1 year and patients who received it after 6 months. Data will be analysed using StataMP 15.1.

### SHI-claim data

#### Sampling

Claim data will be used to assess and compare the costs and use of health services between MamBo patients and patients in standard care. For this purpose, the SHI “PronovaBKK” provides anonymised claim data of the MamBo-population. A statistical twin with data available to the German Health Risk Institute (HRI) [31] is determined for each MamBo participant using the propensity score matching (PSM) method [32]. Matching is performed by the HRI according to criteria such as age, gender and diagnosis.

A sample size of *n* = 2617 corresponding to a statistical power of 79.2% was aimed, given an unpaired t-test, a Cohen’s d of 0.068 and a significance level of 0.05. However, the patients’ enrolment did not correspond to the expected sample size goals, which caused reduced statistical power. To ensure maximum statistical power, the evaluation design of the SHI-claim data analysis has been adopted to the different temporal availabilities of the key parameters. One part can be delivered within 3 months. The other part is available with a delay of up to 9 months. Therefore, group 1 (*n* = 1.975) was closed on 01.04.2019 and group 2 (*n* = 2365) was closed on 01.10.2019. By this, sufficiently high power is guaranteed. The power for Group 1 is about 68% and for Group 2 about 76%.

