#### Data collection and analysis

Both patient-related (e.g. improvements of care,) as well as payer-related (e.g. hospitalizations, utilization of outpatient care) objectives will be considered in the analysis. With MamBo a mean cost reduction of 12,5% is expected due to reduced hospitalization rates. For all variables, a comparison is made between the intervention group and the twin group with significance tests. The selection of the appropriate statistical test depends, among others, on the type (binary/continuous) and distribution of the respective variables.

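### The claims-data powers (79.2%, about 68%, about 76%) rest on an undeclared one-sided 5% test, and the assurance of sufficient power is unsupported whether the test is one- or two-sided

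*Protocol article*

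**What the plan says.** The protocol article, under SHI-claim data, Sampling, sets a target of n = 2617 "corresponding to a statistical power of 79.2% was aimed, given an unpaired t-test", with a Cohen's d "of 0.068 and a significance level of 0.05". One statistical twin "is determined for each MamBo participant using the propensity score matching (PSM) method", which makes the comparison 1:1.

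The section then reports that enrolment fell short and power was reduced. Because some data arrive later than others, two groups were closed at different dates, Group 1 with n = 1975 and Group 2 with n = 2365. It concludes: "By this, sufficiently high power is guaranteed". The next sentence reads: "The power for Group 1 is about 68% and for Group 2 about 76" per cent. Table 1, under Setting, gives Group 2 as about 2524.

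Under SHI-claim data, Data collection and analysis, the article says that "a mean cost reduction of 12,5% is expected due to reduced hospitalization rates". On testing it says: "For all variables, a comparison is made between the intervention group and the twin group with significance tests". The choice of test depends on, among other things, variable type and distribution. Neither section says whether the tests are one- or two-sided.

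**The concern.** The article prints the test, the effect size, alpha, the sample sizes and the powers, and draws a conclusion from them. It omits the one input that moves every power by about 10 to 11 percentage points. Most readers take an unqualified 5% level as two-sided and would believe the analysis stronger than it is.

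The claims analysis is the only comparison of MamBo patients with patients outside the programme, since the non-treatment group in the patient survey is itself enrolled. Its results are meant to inform the decision on transfer to standard care. If power is overstated, a non-significant result is more easily taken as evidence that the model has no effect. The assurance of sufficient power, placed beside two figures below the plan's own target, adds to that risk.

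**Working it through.** **Inputs** (SHI-claim data, Sampling, unless noted): unpaired t-test; d = 0.068; alpha = 0.05; one twin per participant, so n is the number per group; n = 2617 (target), 1975 (Group 1), 2365 (Group 2); Table 1 has 2524 for Group 2.

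**Formula.** Power ≈ Φ(d·√(n/2) − z), with z = 1.645 for one-sided 5% and z = 1.960 for two-sided 5%. The exact noncentral t gives the same results to the first decimal, apart from differences of 0.1 point or less.

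**Reproducing the stated figures.** For n = 2617: 0.068 × √1308.5 = 2.460.
- One-sided: Φ(2.460 − 1.645) = Φ(0.815) = 79.2%, the stated value to the decimal.
- Two-sided: Φ(2.460 − 1.960) = Φ(0.500) = 69.1%.

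| n per group | d·√(n/2) | Stated | One-sided 5% | Two-sided 5% |
|---|---|---|---|---|
| 2617 (target) | 2.460 | 79.2% | 79.2% | 69.1% |
| 1975 (Group 1) | 2.137 | about 68% | 68.9% | 57.0% |
| 2365 (Group 2, Sampling) | 2.338 | about 76% | 75.6% | 64.7% |
| 2524 (Group 2, Table 1) | 2.416 | – | 78.0% | 67.6% |

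The one-sided value for Group 1 would round to 69, so it agrees with the stated figure only approximately. The other two agree to the precision given.

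**Other readings tried.**
- n as the total of both arms: for 2617, 53.8% one-sided and 41.3% two-sided. Neither fits.
- A paired test with d as the standardised within-pair difference: 96.7%, 91.6% and 95.2% one-sided; 93.6%, 85.6% and 91.1% two-sided. Neither fits.
- Two-sided with d anywhere that rounds to 0.068 (0.0675 to 0.0685): at most 69.8%, 57.6% and 65.4%. A two-sided test would need d of about 0.077 to 0.078 to reach the stated powers.
- Two-sided with two controls per participant: 81.1%, 69.4% and 77.0%. This is within 2 points but does not give 79.2%, and the one-twin design excludes it.

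**Against the plan's own target.** One-sided, the stated powers are 79.2 − 68 = 11.2 and 79.2 − 76 = 3.2 points short. Two-sided, the shortfalls are 79.2 − 57.0 = 22.2 and 79.2 − 64.7 = 14.5 points (79.2 − 67.6 = 11.6 if Group 2 is 2524). A two-sided test with 79.2% power needs n = 2 × ((1.960 + 0.813)/0.068)² ≈ 3327 per group.

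**Detectable effect at 80% two-sided power.** d = 2.80 × √(2/n) gives 0.089 for Group 1 and 0.081 for Group 2 (n = 2365). Only if d = 0.068 is assumed to represent the 12.5% cost reduction do these become 12.5% × 0.0892/0.068 ≈ 16.4% and 12.5% × 0.0815/0.068 ≈ 15.0%.

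**The case against.** The strongest reply is that nothing here is miscalculated. The printed powers are right for a one-sided test, the expected cost reduction is directional, and a condensed article may leave sidedness to a full protocol or analysis plan. The article also admits reduced power and prints both lower figures openly. It sets no minimum power, so whether power is sufficient is partly a judgement.

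Much of this stands. The figures are not arithmetically wrong, a declared one-sided test would be legitimate, and silence on sidedness alone would not be worth raising. But the article publishes powers that need the missing convention to be understood, and it relies on them for an assurance. The directional expectation concerns cost only, whereas the tests cover all variables, including use of outpatient care, for which no direction is given.

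A reader might infer more than the document supports:
- That the plan is two-sided and therefore contradicts itself. It commits to neither; two-sided is only the usual reading of an unqualified 5% level.
- That Group 1 would miss a true 12.5% saving about 43% of the time. The 43% (100 − 57) is the two-sided miss rate at d = 0.068. The article never links that d to the 12.5%, and it does not say which group carries the cost outcome.
- That a one-sided test is unacceptable because it could not flag a cost increase. That is a reason to prefer a two-sided test, not an error in the document.

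**Conclusion.** The point holds as an undeclared convention together with an unsupported assurance. The stated powers require a one-sided 5% test that the article does not declare. Read two-sided, they fall to about 69% for the target n, 57% for Group 1 and 65% for Group 2 (68% with the Table 1 figure). The claim of sufficient power fails on both readings when measured against the plan's own 79.2%, by about 3 to 11 points on the stated figures and by about 12 to 22 points two-sided.

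This rests on 1:1 matching, d = 0.068 and the unpaired t-test used in the plan's own calculation. Power for variables analysed with other tests may differ. The percentage savings of 16.4% and 15.0% are illustrative only, because they depend on a link between d and the cost reduction that the document does not state.

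**What to change.** 1. Under SHI-claim data, Sampling, state whether the test is one- or two-sided. Give power as about 69% (n = 2617), 57% (Group 1) and 65% (Group 2, n = 2365), unless a one-sided 5% test is explicitly declared, justified and applied in the analysis.
2. Before restating the Group 2 power, reconcile its sample size: 2365 under Sampling against about 2524 in Table 1. With 2524 the two-sided figure is about 68%.
3. Replace the assurance of sufficient power with a statement that power is reduced, and that a non-significant result will be read from its confidence interval and not as absence of effect.
4. If power is to be expressed as a percentage cost saving, first state whether d = 0.068 represents the 12.5% reduction and which group carries the cost outcome.

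The cost is wording and a less favourable published power. No further patients are needed.

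### The claims-data power assumes independent patients, although about 40 physicians enrol the whole MamBo arm, so the assurance of sufficient power is not supported

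*Protocol article*

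**What the plan says.** All places are in the Protocol article.

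- SHI-claim data, Sampling: a sample of 2617, "corresponding to a statistical power of 79.2% was aimed, given an unpaired t-test", with d = 0.068 and alpha 0.05. Enrolment fell short: "group 1 (*n* = 1.975) was closed on 01.04.2019 and group 2 (*n* = 2365) was closed on 01.10.2019". The article then says "The power for Group 1 is about 68% and for Group 2 about 76" per cent, and presents this as assured, sufficient power. The comparator is a statistical twin that "is determined for each MamBo participant using the propensity score matching (PSM) method", drawn from data held by the German Health Risk Institute.
- Setting: "it is estimated that approx. 40 physicians and approx. 160 practice staff will participate in the care model". These physicians recruit the MamBo patients.
- Quantitative evaluation design: whether a patient gets a MoniKa home visit, a call or no contact depends on the doctor's assessment as well as the patient's wishes.
- SHI-claim data, Data collection and analysis: intervention and twin groups are compared by significance tests, chosen by variable type and distribution among other things.
- Questionnaire data, Data collection and analysis: "The quantitative data will be analysed using regression-based methods".

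The article mentions no ICC, design effect or physician-level term.

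**The concern.** Selection into the programme, the intensity of MoniKa support and the organisational changes in the practice all run through the physician. Costs and service use of patients under one physician may therefore resemble each other. The MamBo mean then carries less information than the same number of unrelated patients would give. The twins come from a wider pool, so the effect falls mainly on one arm.

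The assumed effect is very small (d = 0.068), so modest variance inflation matters, and the achieved power is already below the original target. Both groups are closed, so the sample cannot be enlarged. What is at stake is how the result is read: a non-significant cost comparison would be judged against more power than the design may have, in an evaluation meant to inform transfer to standard care.

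**Working it through.** **Inputs.** From SHI-claim data, Sampling: d = 0.068, alpha 0.05, n = 2617 planned, 1975 (group 1) and 2365 (group 2) achieved, one twin per participant. (Table 1 gives about 2524 for group 2; I use 2365, which stands beside the power statement.) From Setting: about 40 physicians. The ICC is not given; 0.001 to 0.02 is my assumption.

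**Step 1: reproduce the article's figures.** With n per group, SE = √(2/n) in standard-deviation units and one-sided power = Φ(d/SE − 1.645):

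- n = 2617: 0.068/0.02764 = 2.460, power 79.2% (stated 79.2%)
- n = 1975: 0.068/0.03182 = 2.137, power 68.9% (stated about 68%)
- n = 2365: 0.068/0.02908 = 2.338, power 75.6% (stated about 76%)

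No clustering allowance is needed to reach these values, so the design effect used was 1. Two-sided, the same inputs give 69.1%, 57.0% and 64.7%, which do not match. Sidedness is unstated and is a separate matter; I stay on the one-sided basis so that the loss shown is due to clustering alone.

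**Step 2: cluster the MamBo arm only.** Patients per physician m = 1975/40 = 49.4 and 2365/40 = 59.1. DE = 1 + (m − 1) × ICC, and SE = √((DE + 1)/n).

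Example, group 1, ICC 0.01: DE = 1 + 48.4 × 0.01 = 1.48; SE = √(2.48/1975) = 0.0355; 0.068/0.0355 − 1.645 = 0.27; power 60.7%.

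| Assumed ICC | Group 1: DE | Group 1: power | Group 2: DE | Group 2: power |
|---|---|---|---|---|
| 0 | 1.00 | 68.9% | 1.00 | 75.6% |
| 0.001 | 1.05 | 68.0% | 1.06 | 74.5% |
| 0.005 | 1.24 | 64.6% | 1.29 | 70.5% |
| 0.01 | 1.48 | 60.7% | 1.58 | 66.0% |
| 0.02 | 1.97 | 54.4% | 2.16 | 58.5% |

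**Step 3: allow for the matching.** With outcome correlation ρ within pairs, the variance of the difference is (DE + 1 − 2ρ)/n. It returns to 2/n when ρ = (DE − 1)/2. The correlation that exactly cancels the clustering is:

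- ICC 0.005: 0.12 (group 1), 0.15 (group 2)
- ICC 0.01: 0.24, 0.29
- ICC 0.02: 0.48, 0.58

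The article gives no ρ either.

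**Step 4: conditional type I error.** If the unpaired t-test were also the analysis, and ρ were zero, a nominal one-sided 5% test would have true size 1 − Φ(1.645/√((DE + 1)/2)). For ICC 0.005 to 0.02 this is 6.0–8.8% in group 1 and 6.2–9.5% in group 2. A positive ρ would lower these values.

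**The case against.** Four points on the other side have weight.

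- **The analysis is not fixed.** A reader might infer that the planned tests themselves ignore clustering and that the reported standard errors will be too small. The documents do not support that. The unpaired t-test is named only as a premise of the power calculation. The analysis section leaves the test open, and a full analysis plan could use clustered errors or a physician effect. The type I error figures are therefore conditional.
- **The survey is different.** A reader might carry the same inflation over to the survey models. It does not carry over: patients with and without MoniKa contact share physicians, contact is decided patient by patient, and difference-in-differences removes stable level differences between physicians. The survey text fixes no variance estimator. I claim no figure there.
- **Matching works the other way.** An unpaired calculation that ignores positive pair correlation is conservative. At the low end of the ICC range, a correlation of about 0.12 to 0.15 cancels the loss. This stands, but an unstated correlation cannot support an assurance of power.
- **The ICC and the cluster unit are assumptions.** At ICC 0.001 almost nothing is lost. The cluster size is taken from physicians; the physician survey asks about joint practices, so the number of practices is unknown. If practices are the real unit and are fewer than 40, clusters are larger and the loss at a given ICC is greater.

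**Conclusion.** The point holds for the power statement. The stated 79.2%, 68% and 76% rest on independent patients, which the design does not support. For an unpaired comparison without pair correlation, any positive ICC lowers them. On the article's own one-sided basis, with 40 equal clusters in the MamBo arm only and an assumed ICC of 0.005 to 0.02, clustering costs about 4 to 14 points in group 1 (68.9% to 64.6–54.4%) and about 5 to 17 points in group 2 (75.6% to 70.5–58.5%). The net loss may be smaller or nil if outcomes correlate within pairs, and larger if list sizes are unequal. The documents cannot settle the size, so the claim that sufficient power is assured should not stand. Comparing the stated 68% with a two-sided clustered figure would blame clustering for the separate question of sidedness.

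**What to change.** - Restate the claims-data power over a stated range of ICC and within-pair correlation, and withdraw the wording that sufficient power is guaranteed.
- Ask for a pseudonymous code for the enrolling physician or practice with the claims delivery. The article describes the claims as anonymised and the network's process data as aggregated, so the evaluators may otherwise have no cluster identifier, and a later analysis plan could not repair that.
- Analyse the claims comparison with standard errors that respect both the enrolling practices and the matched pairs, with a small-sample correction based on the actual number of practices.

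Cost: a small change to the data delivery, to be agreed with the data holders; probably wider confidence intervals; and a lower stated power.
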